After determining full eligibility, participants will be enrolled in the trial by providing written informed consent. After completing baseline assessments, participants will be randomly assigned in a 1:1 ratio to the intervention or active control condition using block randomization alternating between varying block sizes of 4, 6, or 8. The principal investigator created a random allocation table using Sealed Envelope, after which it was uploaded to REDCap to define the randomization model of *¡Alégrate!* to ensure proper blocking and stratification by sex (male and female) and use of antihypertensive medication (yes and no). A trained research staff generated allocation assignment through REDCap. It should be noted that REDCap conceals the allocation table and associated sequencing from research staff to prevent selection bias. Finally, given the pilot nature of a Phase II trial, blinding occurs only at the level of data analysis.

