Given our design and main objective of treatment evaluation, an intent-to-treat analysis will be conducted, where we will consider the data of all participants randomized, with retention of their original intervention assignment. Sensitivity analysis will use multiple imputation procedures across missing values to ensure inclusion of all observations, particularly those resulting from participants who withdraw, are lost to follow-up, or do not complete all assessments. In a supplementary analysis, we will use ordinary or logistic regression (as appropriate, given variable distribution) to implement a dose-response analysis to test whether participation-related factors (eg, number of sessions viewed, rate of homework completion) impact outcomes of interest.

We estimated the sample size requirements of a two-arm randomized trial to evaluate whether our web-based positive psychological intervention resulted in differential and clinically meaningful improvements in systolic BP of 6 mm Hg compared with an attention control condition. A repeated-measures design with systolic BP determination at baseline and 5 and 12 weeks was used. In addition, the following operating characteristics were assumed: (1) a between-subject standard deviation for BP of *σ=12 mm Hg*; (2) a within-subject correlation, *ρ=0.60* (3) a two-sided type I error probability of 0.05; and (4) 80% statistical power. Frison and Pocock [65] argue that adjusting for baseline measures (analysis of covariance) results in a more efficient analysis for a given sample size (larger statistical power). This approach yields an estimate of the required sample size of 28 participants per study arm under equal allocation. Furthermore, assuming a conservative attrition rate of 20%, an updated estimation produces the following sample size of participants per study arm.

[figure not shown]

Stata 15 was used for sample size calculation (*sampsi* command) and all statistical analyses, with effect size estimation derived from published data on the clinical effectiveness of psychotherapeutic interventions to treat hypertension [47,66,67].

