#### Aim 1: Determine the Efficacy of the ¡Alégrate! Web-Based Positive Psychological Intervention in Improving BP Control in Hispanic/Latino People With Hypertension From Baseline, Immediately Postintervention (5 Weeks), and at 12 Weeks After Baseline 

Independent samples *t* tests will be performed using 5-week systolic BP and diastolic BP as the dependent variables, with treatment condition serving as the grouping variable. Other model-based approaches to handle missing data, such as weighted estimating equations, will be implemented. We will also use mixed-effects models to compare changes in BP between the control and intervention arms as measured at baseline, 5 weeks, and 12 weeks. The independent variables include a time variable t (t=0, 5, 12), a dummy variable N (N=1, if PP intervention group; N=0, if attention control), and a cross-product term (t×N). For ambulatory data collected across a 24-hour period, sensitivity analyses will compare mean overall daytime versus nighttime values of BP. All data analyses were conducted using SAS 9.4 software (SAS Institute).

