#### Aim 2: To Test Intervention Effects on Psychological Well-Being and Adherence to Healthy Behaviors and to Subsequently Explore Whether Improvements in Psychological Well-Being and Adherence to Healthy Behaviors Are Responsible for Better BP Control, That Is, Mediation Testing

Similar analytic techniques will be implemented for Aim 2 as used for Aim 1. The interaction of Group×Time will test if greater improvements are evident for psychological well-being and engagement in healthy behaviors (eg, dietary intake and self-reported physical activity) at 5 weeks postbaseline for the treatment arm as compared with the active control group. RM-ANOVA will also be used to examine whether the *¡Alégrate!* intervention is associated with greater improvements in psychological well-being and engagement in healthy behavior. In addition to reporting nominal *P* values, we will document the number of tests conducted and associated Bonferroni correction. Finally, we will conduct mediation analysis to test whether psychological well-being and healthy behaviors serve as intermediates (or mediators) through which *¡Alégrate!* impacts BP control. Tests of mediation will follow the recommendations of Shrout and Bolder to bootstrap product terms using Mplus. Given the dependency of indirect effects on the time interval, for multiwave models, we will compute overall, rather than time-specific, indirect effects.

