#### Aim 3: Evaluate Intervention Effects on High-Sensitivity C-Reactive Protein

Similar analytic techniques as previously described will be used when testing intervention effects on chronic inflammation. Specifically, the term capturing Group×Time interaction will test whether lower levels of inflammation are evident at 8 weeks postbaseline for the intervention group versus the active control arm.

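### The trial is sized on baseline-adjusted ANCOVA, but neither Aim 1 blood pressure analysis adjusts for baseline that way; a separate baseline mean for each arm alone costs about 13 points of power

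*Protocol article*

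**What the plan says.** The Planned Analyses section of the protocol article sets the target as "differential and clinically meaningful improvements in systolic BP of 6 mm Hg compared with an attention control condition", with measurements at baseline, 5 and 12 weeks. It justifies the method by citing the argument that "adjusting for baseline measures (analysis of covariance) results in a more efficient analysis for a given sample size (larger statistical power"), and arrives at 28 per arm before attrition.

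The Aim 1 section then names the analyses:

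- independent-samples t tests on 5-week systolic and diastolic BP by arm;
- weighted estimating equations for missing data, with no visits or covariates given;
- a mixed-effects model of BP at baseline, 5 and 12 weeks, with a time variable coded 0, 5, 12, "a dummy variable N (N=1, if PP intervention group; N=0, if attention control), and a cross-product term (t×N").

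On timing, the Consent, Assessments, and Randomization section says: "After completing baseline assessments, participants will be randomly assigned in a 1:1 ratio". Baseline BP is therefore a pre-randomisation value.

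Baseline BP is not named as a prespecified covariate anywhere. The covariate list in Table 2 does not contain it, and the only rule for adding covariates in Planned Analyses is that observed baseline discrepancies between arms will guide the choice.

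**The concern.** The sample size takes credit for the precision that baseline adjustment brings, and the analyses listed for Aim 1 do not collect it. The t test ignores baseline and week 12. The mixed model uses baseline, but as one more outcome with its own mean in each arm. With N in the model, the treatment effect is read from t×N, a contrast of change within participants. Any arm difference at t=0 is chance, because baseline precedes randomisation. Subtracting it in full, rather than in proportion to its correlation with follow-up, adds its noise to the treatment estimate.

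At stake is the chance of detecting the effect for which the trial was designed, in a trial of 70 people with no margin beyond the attrition allowance.

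**Working it through.** **Inputs** (Planned Analyses): difference 6 mm Hg, SD 12, within-subject correlation ρ=0.60, two-sided 5%, 80% power, one baseline and two follow-up visits, 28 analysed per arm. *Assumption:* equal correlation between every pair of visits, since a single ρ is given. Normal approximation throughout.

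**Formulas.** For a contrast with variance factor f:

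- SE = √(2·144·f/n)
- power = Φ(6/SE − 1.96)
- n per arm = 2·(1.96+0.8416)²·(12/6)²·f = 62.79·f

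**Step 1: reproduce the plan.** ANCOVA on the mean of two follow-ups has f = (1+ρ)/2 − ρ² = 0.80 − 0.36 = 0.44.

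- n = 62.79·0.44 = 27.6, so 28 per arm.
- SE = √(126.72/28) = 2.13; power = Φ(2.82 − 1.96) = 80.5%.
- 20% attrition: 28/0.80 = 35 per arm, 70 in total, as stated in the Abstract.

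The arithmetic is right for ANCOVA.

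**Step 2: the 5-week t test.** f = 1; SE = √(288/28) = 3.21; power = Φ(1.87 − 1.96) = 46.4%. It would need 63 per arm.

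**Step 3: the effect of N alone.** Keep visits categorical and average weeks 5 and 12, but let each arm have its own baseline mean. The estimate is then mean follow-up minus baseline, with f = (1+ρ)/2 + 1 − 2ρ = 0.80 + 1 − 1.20 = 0.60.

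- SE = √(172.8/28) = 2.48; power = Φ(2.42 − 1.96) = 67.6%.
- n = 62.79·0.60 = 37.7, so 38 per arm (48 after 20% attrition).
- Interval width relative to Step 1: √(0.60/0.44) = 1.17.

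**Step 4: the model as written.** With one numeric t and one t×N term, the test compares slopes. For t = 0, 5, 12 the mean is 5.67 and the sum of squared deviations is 72.67. With N in the model, SE(slope difference) = √(2·144·0.40/(28·72.67)) = 0.238. A constant 6 mm Hg effect at both visits gives an expected slope difference of 34/72.67 = 0.468, so power is 50.3%. Without N, generalised least squares gives 0.514 (SE 0.214), power 67.3%.

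Power at 28 per arm, constant 6 mm Hg effect:

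| Time coding | N free | Common baseline mean |
|---|---|---|
| Categorical, average of weeks 5 and 12 | 67.6% | 80.5% |
| Linear t, slope difference | 50.3% | 67.3% |

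**Step 5: other effect patterns**, model as written (linear t, N included), 28 per arm:

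| Effect pattern | Power |
|---|---|
| Linear growth to 6 at week 12 | 55.6% |
| Linear growth averaging 6 (about 3.5 at week 5, 8.5 at week 12) | 84.3% |
| 6 at week 5, fading to 3 at week 12 | 13.7% |

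**Step 6: sensitivity.**

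- Averaged contrast, common baseline against free N: 75% and 58% at ρ=0.5; 88% and 80% at ρ=0.7; 96% and 93% at ρ=0.8.
- With all 35 per arm retained and ρ=0.60: free N on the averaged contrast 77.0%, linear slope with a constant effect 59.4%, t test 55.2%.
- Baseline-adjusted contrast at a single visit, f = 1 − ρ² = 0.64: power 64.7% at 28 per arm.

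**The case against.** The strongest defence has four parts.

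**The article is condensed and names no primary analysis.** The mixed model follows the t tests as an additional method, its listed terms may not be exhaustive, and weighted estimating equations are also mentioned, so it cannot be called the only three-visit analysis. This lowers certainty about the final model. It does not remove the mismatch: the terms that are listed conflict with the sizing method, and adding covariates after seeing an imbalance is not prespecified baseline adjustment.

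**The analysis is valid.** This stands. Under randomisation, a group-by-time test with free baseline means is unbiased. The loss is one of efficiency, and it shrinks to 3 points at ρ=0.8.

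**A reader might infer that the N term brings power down from 80% to 50%.** The figures do not support that. The 50.3% needs linear time coding and a constant effect as well as the N term. In the other direction, 67.6% and the 17% wider interval belong to categorical visits averaged over weeks 5 and 12, which is not the written slope test. The written test runs from 14% to 84% across the patterns in Step 5, and the article does not say which pattern is expected.

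**The 80% comparator depends on a contrast that the article never names.** This also stands. Aim 1 asks about efficacy at 5 weeks and at 12 weeks; the 28 per arm holds for their average. Even with full baseline adjustment, either visit alone has about 65% power.

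**Conclusion.** The point holds as a mismatch between the analysis that was powered and the analyses that are listed. The sample size arithmetic is correct for baseline-adjusted ANCOVA, and neither the t test nor the mixed model with its listed terms is that analysis.

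The size attributable to separate baseline means is about 13 points on the averaged contrast (80.5% to 67.6%), or 10 more participants per arm. On that contrast, a true 6 mm Hg effect would be missed in about one trial in three rather than one in five. This rests on SD 12, ρ=0.60, equal correlations and 28 analysed per arm. The linear coding of time is a further, separate loss when the effect is constant, and its size cannot be fixed without an assumed effect pattern.

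A reader might extend the finding to Aims 2 and 3, where "The interaction of Group×Time will test if greater improvements are evident for psychological well-being and engagement in healthy behaviors" and where "the term capturing Group×Time interaction will test whether lower levels of inflammation are evident". The same model structure appears there, but the article states power for systolic BP only. No stated power is missed, and no correlation is given from which to size a loss.

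**What to change.** Either of two forms restores agreement with the sample size:

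- analyse week 5 and week 12 BP with arm, visit, arm×visit and baseline BP as a prespecified covariate; or
- equivalently, keep all three visits as responses in a constrained longitudinal model with categorical visit, one baseline mean shared by both arms, and arm-by-visit terms after baseline only.

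In both, name the arm contrast averaged over weeks 5 and 12 as the powered effect, and report the week 5 and week 12 contrasts with their lower power (about 65% each at 28 per arm). Merely deleting N while t stays linear is not enough: under a constant 6 mm Hg effect it leaves 67.3%.

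If the listed analyses are kept, restate the power for whichever is primary, with the effect pattern assumed for the slope test.

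The cost is a changed model specification, a few sentences, and an explicit decision on the averaged contrast, settled before outcome data are examined by arm. No new data, visits or participants are needed, and randomisation justifies the common baseline mean. Using the same baseline-adjusted form in Aims 2 and 3 is an optional efficiency gain.

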#### Aim 2: To Test Intervention Effects on Psychological Well-Being and Adherence to Healthy Behaviors and to Subsequently Explore Whether Improvements in Psychological Well-Being and Adherence to Healthy Behaviors Are Responsible for Better BP Control, That Is, Mediation Testing

Similar analytic techniques will be implemented for Aim 2 as used for Aim 1. The interaction of Group×Time will test if greater improvements are evident for psychological well-being and engagement in healthy behaviors (eg, dietary intake and self-reported physical activity) at 5 weeks postbaseline for the treatment arm as compared with the active control group. RM-ANOVA will also be used to examine whether the *¡Alégrate!* intervention is associated with greater improvements in psychological well-being and engagement in healthy behavior. In addition to reporting nominal *P* values, we will document the number of tests conducted and associated Bonferroni correction. Finally, we will conduct mediation analysis to test whether psychological well-being and healthy behaviors serve as intermediates (or mediators) through which *¡Alégrate!* impacts BP control. Tests of mediation will follow the recommendations of Shrout and Bolder to bootstrap product terms using Mplus. Given the dependency of indirect effects on the time interval, for multiwave models, we will compute overall, rather than time-specific, indirect effects.

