#### Secondary Outcomes

*Table 2* identifies the secondary outcomes and describes in detail the survey and clinical measures used to capture these constructs. Specifically, secondary outcomes include the following: (1) psychological well-being (depressive symptoms, perceived stress, positive and negative affect, optimism, emotional vitality, life engagement and meaning, happiness-inducing behavior, and social support), (2) healthy behaviors (physical activity, diet, sodium intake, smoking status, sleep quality and duration, and mediation use), and (3) biological materials (serum blood spots).

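### Aim 2 sets nominal P values beside a Bonferroni correction whose divisor is not fixed, while overlapping methods test the same outcomes and neither result is named as governing

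*Protocol article*

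**What the plan says.** **Outcomes.** The Secondary Outcomes section of the protocol article lists two groups relevant to Aim 2. The first is "1) psychological well-being (depressive symptoms, perceived stress, positive and negative affect, optimism, emotional vitality, life engagement and meaning, happiness-inducing behavior, and social support", which makes eight items. The second, healthy behaviours, has six: physical activity, diet, sodium intake, smoking status, sleep quality and duration, and medication use.

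**Methods.** The Aim 2 section applies techniques similar to those of Aim 1. In the Aim 1 section these are independent-samples t tests at 5 weeks and mixed-effects models over 0, 5 and 12 weeks. Aim 2 then specifies a Group×Time interaction at 5 weeks, and adds that "RM-ANOVA will also be used to examine whether" the intervention improves the same outcomes.

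**Multiplicity.** In addition to nominal P values, "we will document the number of tests conducted and associated Bonferroni correction". No number of tests, adjusted threshold or governing result is given.

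**Status of the aim.** The wording is mixed. The opening of Planned Analyses describes the second aim as exploring improvements. The Introduction hypothesises them, and the Aim 2 heading speaks of testing effects and keeps exploration for the mediation step.

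**The concern.** A Bonferroni correction is only as definite as its divisor. Here the divisor depends on how many outcomes are counted and on whether a t test, a mixed-model interaction and an RM-ANOVA of one outcome count as one test or as several. An outcome with P = 0.002 passes over 14 tests (threshold 0.0036) and fails over 42 (threshold 0.0012). An outcome with P = 0.02 is significant nominally and fails under either divisor. The text does not say which reading would support an Aim 2 claim.

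At stake is the credibility of the secondary results. Relying on nominal values makes a false positive somewhere among the outcomes quite likely. Counting several tests of one hypothesis separately spends power for no gain in error control.

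**Working it through.** **1. The plan's own figure.** Inputs from Planned Analyses: a difference of 6 mm Hg, SD 12 mm Hg, within-subject correlation 0.60, "a two-sided type I error probability of 0.05", "80% statistical power", one baseline and two follow-ups.

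- Variance factor for baseline-adjusted analysis: (1 + (r−1)ρ)/r − ρ². With r = 2 this is 1.6/2 − 0.36 = 0.44.
- n per arm = 2 × 12² × (1.960 + 0.842)² / 6² × 0.44 = 27.63, so 28.
- With 20% attrition: 28/0.8 = 35 per arm, 70 in total.

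The stated 28 per arm and the total of 70 reproduce. That calculation concerns systolic BP only; the article gives no power for Aim 2.

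**2. Range of the divisor.** One test per listed item gives 8 + 6 = 14. Splitting positive from negative affect, and sleep quality from sleep duration, gives 16. Two methods per outcome give 28-32 and three give 42-48. The count of methods is an assumption.

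**3. Per-outcome power.** Assumptions: a true effect of 0.5 SD (the BP design effect, 6/12), correlation 0.60, 28 evaluable per arm, and a baseline-adjusted 5-week comparison of a continuous outcome. With one follow-up the variance factor is 1 − 0.36 = 0.64.

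- SE = √(2 × 0.64/28) = 0.214 SD, so the expected z is 0.5/0.214 = 2.34.
- Power = Φ(2.34 − critical z) at two-sided level 0.05/m.

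| Rule | Level | Power, 5 weeks | Power, both follow-ups (factor 0.44) |
|---|---|---|---|
| Nominal | 0.05 | 65% | 81% |
| Bonferroni, m = 14 | 0.00357 | 28% | 46% |
| Bonferroni, m = 16 | 0.00313 | 27% | 45% |
| Bonferroni, m = 28 | 0.00179 | 22% | 38% |
| Bonferroni, m = 42 | 0.00119 | 18% | 34% |

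**4. Holm over 14.** Holm compares the smallest P value with 0.05/14, the next with 0.05/13, and so on until one fails. By simulation (40,000 runs, correlation between outcomes 0 and 0.4), 5-week power per truly affected outcome is:

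- 28% with 1 outcome affected, 29% with 4, 30% with 7;
- 33-35% with all 14 affected.

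Over Bonferroni at m = 14, Holm thus adds 0-2 points when up to half the outcomes are affected and 4-7 points if all are. With both follow-ups the gains are 0-3 and 10-11 points. Going from 42 tests to 14 under Bonferroni adds 28 − 18 = 10 points (46 − 34 = 12 with both follow-ups).

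**5. If nominal values governed.** With 14 independent true nulls, the chance of at least one P < 0.05 is 1 − 0.95^14 = 51%. By simulation (20,000 runs) it is 44% at a between-outcome correlation of 0.3 and 35% at 0.5.

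**The case against.** The strongest reply is that this is a reporting sentence for secondary outcomes in a pilot trial. Planned Analyses words the aim as exploratory, no Aim 2 success criterion is stated, and an analysis plan that is not shown may list the family. The article also commits to disclosing nominal values, test count and correction, so readers would see both results. This limits the weight of the point but does not remove it. The article does state a multiplicity rule, and as stated the rule determines neither its divisor nor its authority. The Introduction and the Aim 2 heading also frame these effects as hypothesised and tested.

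Three stronger readings are tempting and should not be drawn:

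- **That the test count will be settled after the data are seen, or that each outcome will be counted three times.** The text says only that the number of tests will be documented. A divisor of 42 is a worst case: the t test comes in only through the reference to similar techniques, and Group×Time is itself the treatment test within an RM-ANOVA.
- **That repeat counting is why real effects would be missed.** Over 14 tests with no repeats, power is still only 28%. The main causes are the number of outcomes and 28 per arm.
- **That Holm restores the lost power.** It adds little unless most outcomes are affected.

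Nor do the documents make the mediation analysis conditional on Aim 2 P values; it rests on bootstrapped product terms.

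**Conclusion.** The point holds as a defect of specification: the Aim 2 text leaves both the Bonferroni divisor and the governing result undetermined, with overlapping tests of the same outcomes and none named as main. Under the stated assumptions the choice of divisor moves per-outcome power between about 28% and 18% at 5 weeks, and reliance on nominal values would carry a 35-51% chance of at least one false positive among 14 null outcomes.

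The power figures rest on an assumed 0.5 SD effect and on a correlation and sample size taken from the BP calculation. They describe continuous outcomes only, so they do not apply to smoking status, and adherence is measured only in participants on antihypertensive medication. Even after correction, power for a single Aim 2 outcome stays low. The primary BP conclusions are not affected.

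**What to change.** 1. Name one main analysis per Aim 2 outcome: the baseline-adjusted between-arm difference at 5 weeks, with a model suited to non-continuous outcomes such as smoking status.
2. List the family before analysis. Settle whether affect and sleep each count as one outcome or two, and how adherence among medicated participants enters.
3. Replace Bonferroni with Holm over that family, and let the Holm-adjusted P values govern any Aim 2 claim. Holm controls the same familywise error rate under the same conditions and never rejects less.
4. Report nominal P values as descriptive, and t tests and RM-ANOVA as sensitivity results that carry no claim.

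The cost is about one paragraph and no new data. Data collection was still under way when the article was written, so the change could precede the analysis. The downside is that no Aim 2 claim can then rest on a nominal P value or on the most favourable of several methods.
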